## Abstract

**Background:**

Women who develop secondary arm lymphoedema subsequent to treatment associated with breast cancer require life-long management for a range of symptoms including arm swelling, heaviness, tightness in the arm and sometimes the chest, upper body impairment and changes to a range of parameters relating to quality of life. While exercise under controlled conditions has had positive outcomes, the impact of yoga has not been investigated. The aim of this study is to determine the effectiveness of yoga in the physical and psycho-social domains, in the hope that women can be offered another safe, holistic modality to help control many, if not all, of the effects of secondary arm lymphoedema.

**Methods and design:**

A randomised controlled pilot trial will be conducted in Hobart and Launceston with a total of 40 women receiving either yoga intervention or current best practice care. Intervention will consist of eight weeks of a weekly teacher-led yoga class with a home-based daily yoga practice delivered by DVD. Primary outcome measures will be the effects of yoga on lymphoedema and its associated symptoms and quality of life. Secondary outcome measures will be range of motion of the arm and thoracic spine, shoulder strength, and weekly and daily physical activity. Primary and secondary outcomes will be measured at baseline, weeks four, eight and a four week follow up at week twelve. Range of motion of the spine, in a self-nominated group, will be measured at baseline, weeks eight and twelve. A further outcome will be the women’s perceptions of the yoga collected by interview at week eight.

**Discussion:**

The results of this trial will provide information on the safety and effectiveness of yoga for women with secondary arm lymphoedema from breast cancer treatment. It will also inform methodology for future, larger trials.

**Trial registration:**

ACTRN12611000202965

## Background

Breast cancer- related lymphoedema (BCRL) is a result of disruption to the lymphatic transport system as a result of a number of procedures associated with the treatment of breast cancer [1]. BCRL is associated with chronic or recurring swelling of the affected area and underlain by cellular and tissue changes, making the area more prone to infections. High risk indicators for lymphoedema onset are mastectomy, radiation to the axilla, axillary dissection and removal of a high number of lymph nodes [2]. In spite of recent changes to surgical and radiological procedures for breast cancer, at least 20% of women are still affected [3]. As breast cancer incidence continues to rise [4], a significant number of women will continue to get secondary lymphoedema. While the arm is the most common site, the chest, upper back or breast are also often involved. As these areas are difficult to measure, current incidence rates are likely to be significantly underestimated.

The loss of upper body function can be higher for women with BCRL than for those treated for breast cancer without lymphoedema [5]. Physical activity can be reduced not only due to the swelling, but also as a consequence of the changed sensations [6], pain [7] and fatigue [8], as well as women’s fear of exacerbating the symptoms of lymphoedema [9]. Women commonly report stiffness and impairment in the range of motion of their affected shoulder and limitations in various daily activities that depend on carrying, repetitive actions or having their arm in the same position for a prolonged period [10]. Biomechanics of the thoracic-shoulder area can be compromised [11,12], which can create further upper body impairment. Additionally, women experience feelings of abandonment and isolation, compounded by uncertainty and poor body image [13,14], which can lead to a lowered quality of life in physical, social, personal and emotional domains [15].

BCRL requires early recognition, targeted treatment and self-management for life to reduce the risk of infection and prevent the condition worsening. Treatment may include complex lymphoedema therapy involving manual lymphatic drainage (MLD) with compression bandaging as required, and daily self-management, which focuses on skin care, self-massage, specific exercises with deep breathing and wearing a compression sleeve [16,17]. Motivation and compliance with self-care are difficult to maintain [18] due to treatment fatigue and a feeling of frustration that the limb is not getting significantly better.

Participation in exercise is increasingly recommended as another option for women with BCRL to improve their physical and mental health [19,20]. Guidelines state that supervised exercise with adequate warm-up and cool-down, and gradual progression of intensity or difficulty, may be followed by women with BCRL [21]. This is based on positive results from large randomised controlled trials of resistance training [22,23] and from smaller trials covering a variety of other exercise modalities [24] including combined aerobic and resistance exercise [25], tai-chi [26], gentle exercise with relaxation [27] and aquatic exercise [28]. Importantly, these trials have reported no exacerbation of lymphoedema and an improvement in physical fitness, upper body function and quality of life.

Currently, there is no published research into the effects of yoga on BCRL, despite many women with BCRL stating that they are already using yoga along with conventional lymphoedema treatment [29]. However, yoga therapy as part of a holistic treatment for lower limb lymphoedema in India, has resulted in decreased levels of lymphoedema, and fewer infections. It focuses on lymphatic clearing by using specific postures, deep diaphragmatic breathing, elevation of legs and relaxation [30].

Yoga can offer a holistic approach to the management of BCRL as the practices promote progressive physical postures (*asana*) with breath awareness, breathing exercises (*pranayama*), meditation and relaxation. Research into the efficacy of yoga for women during and after breast cancer treatment (without lymphoedema) reports improved quality of life [31]and immunity [32,33] as well as reduction of pain [34] and fatigue [35]. Other improvements have been reported in flexibility [36], grip strength, shoulder function [37] and body image [38]. These outcomes may be transferrable to women with BCRL.

The aim of this study is to evaluate the effects of an eight-week integrated yoga intervention on women with BCRL. The primary objectives are to evaluate the effect of regular yoga participation on lymphoedema (amount of fluid and tissue density), and its associated symptoms (sensations, pain, fatigue) and to assess its impact on quality of life. Secondary objectives are to determine the effect of yoga on the upper body, in particular shoulder mobility and strength and mobility of the thoracic spine. A further objective is to investigate participant perceptions about the effectiveness of the yoga intervention. Information about daily and weekly physical activity as well as demographic information will also be collected.

We hypothesise that an eight-week integrated yoga intervention will have a beneficial effect on BCRL as indicated by reduced swelling of the affected arm, reduced tissue density, fewer symptoms of pain, fatigue and sensations and their limiting effects, improved quality of life and upper body functioning.

## Methods/design

### Study design and setting

This study is designed to be a randomised controlled trial for women with stage one BCRL, as defined by the International Society of Lymphology [16]. The study will compare the results of a group who receive an integrated yoga intervention, to a control group who will continue to follow current best-practice in self-management of lymphoedema from a manual given to all participants pre-randomisation, but who will receive no yoga intervention. The control group will be wait-listed for the yoga intervention and so will be invited to participate at the completion of the study.

Measurements will be conducted at baseline (week 0), after which participants will be randomised to the yoga intervention or the control group. Further measurements will be made at week 4 (mid-point), week 8 (on completion of the yoga) and at week 12 (four weeks after the intervention).

The trial will be held at two locations, Hobart and Launceston. Both locations will consist of an intervention and control group. The study will be conducted at Community Health Centres in both locations.

### Ethical considerations

The study has been approved by the University of Tasmania Social Sciences Ethics committee. Yearly progress reports will be made to the ethics committee and they will be notified of any adverse events promptly. The trial has been registered with the Australian New Zealand Clinical Trials Registry (ACTRN12611000202965, http://www.anzctr.org.au/default.aspx).

All women in the trial will receive information in a manual specifically developed for this trial on best current practice for management of secondary lymphoedema, based on the guidelines of the Australasian Lymphology Association and Lymphoedema Framework [16,39].

Women will be advised to continue with their usual treatment plan during the trial and to seek medical help in the case of infection or a flare-up of lymphoedema. Should this occur, women will be advised they can continue with the trial but told their measurements will not be included in the results, as it will change their status with regard to the eligibility criteria.

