### Participants

Eligibility criteria based on previous exercise trials for women with BCRL will be followed [26,40]. Criteria for inclusion are completion of treatment for breast cancer in terms of surgery, radiotherapy and chemotherapy at least 6 months previously; unilateral secondary lymphoedema stage one related to surgery for breast cancer, as confirmed by a registered lymphoedema therapist; good English comprehension in order to understand the written forms and oral instructions and be able to give informed consent; aged > 18 years.

Criteria for exclusion are conditions of primary lymphoedema, recurrent cancer and other symptoms including infection or cellulitis, which would affect the woman’s lymphoedema and her quality of life adversely; severe psychological illness, as the yoga intervention would need to be specific to the person’s psychological illness in order to improve it; pregnant women and women with pacemakers, as these conditions are contra-indicated for the use of bio-impedance spectroscopy – one of the measuring tools for this study [41]; current lymphoedema treatment other than self-management, as this would affect the results.

Women will also be asked to refrain from commencing any new physical activity during the term of the trial as this could affect results.

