#### Volume and percentage volume of arm and hand lymphoedema

Circumferential readings will be based on the protocol of the Australasian Lymphology Association [45], modified so the woman is lying not sitting. Both arms will be marked at the metacarpophalangeal joint, ulnar styloid and 10, 20, 30, 40 centimetres (cm) from the styloid process, using a pen and set square on the medial and lateral aspect of the arm, then circumference measured at each point by a Job non-stretch tape, recorded in cm. Finger circumferences will be measured distal to the web space, and recorded in millimetres (mm). Volume of lymphoedema and percentage of lymphoedema in the arm and hand will be calculated using the truncated cone formula [46] from the addition of circumference readings, using software provided by Flinders Lymphoedema Clinic, South Australia (SA), which compares the affected to the non-affected arm. An increase in fluid volume and % fluid volume readings equates to an increase in level of lymphoedema. Fluid volume will be recorded as millilitres (ml) and % fluid volume of ml.

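### Measurements of women who have an infection or lymphoedema flare-up after randomisation are left out of the results, an outcome-dependent exclusion that can hide harm or benefit of yoga

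*Protocol article*

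**What the plan says.** Under Ethical considerations, the protocol article tells women "to seek medical help in the case of infection or a flare-up of lymphoedema". If that happens, "women will be advised they can continue with the trial but told their measurements will not be included in the results", and the reason given is "as it will change their status with regard to the eligibility criteria". The entry exclusions under Participants include "recurrent cancer and other symptoms including infection or cellulitis". A flare-up is not named there, although it could bear on the stage-one requirement or lead to treatment beyond self-management, which is also an exclusion.

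Four other places bear on this rule:

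- **Timing** (Study design and setting): "Measurements will be conducted at baseline (week 0), after which participants will be randomised to the yoga intervention or the control group". Follow-up measurements are at weeks 4, 8 and 12.
- **Primary objective** (Background): "The primary objectives are to evaluate the effect of regular yoga participation on lymphoedema (amount of fluid and tissue density", together with symptoms and quality of life.
- **Direction of the outcome** (Volume and percentage volume of arm and hand lymphoedema): "An increase in fluid volume and % fluid volume readings equates to an increase in level of lymphoedema".
- **Purpose** (Abstract, Discussion): "The results of this trial will provide information on the safety and effectiveness of yoga".

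The Data analysis section contains nothing that brings the excluded women back. Ethical considerations also says that the ethics committee is told promptly of adverse events.

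**The concern.** Entry criteria decide who is randomised. They give no ground for removing a woman's data because of something that happens to her afterwards. Here the triggering event can also be affected by treatment, and a flare-up is a worsening of the quantity that the trial is designed to compare. Infection is linked less directly, since it is not itself a measured primary outcome, but it too is a post-randomisation event.

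After such an exclusion the two arms are no longer the groups that randomisation formed. If yoga provokes flare-ups, the readings that would show it are dropped. If yoga prevents them, the control readings that would show the benefit are dropped. For a trial meant to inform on safety and effectiveness, the main comparison would then omit the women who bear most directly on both.

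**Working it through.** **1. The plan's own figures.** The documents give no rate, size or timing of flare-ups, so there is no figure of the plan to reproduce on this point. The only related numbers are the sample size: 13 to 19 required per group and 20 planned (Sample size calculation). They are not disputed here. One woman is 1/20 = 5% of an arm. The margin over the stated need is 20 − 19 = 1 to 20 − 13 = 7 women per arm, and it was set aside for withdrawals.

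**2. Order of events.** Baseline, then randomisation, then weeks 4, 8 and 12. Any infection or flare-up during follow-up is therefore a post-randomisation event.

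**3. Fixed-shift model (assumption).** Let a flare-up occur with probability p_Y (yoga) or p_C (control), independently of the rest of the outcome, and raise the outcome by s. Higher is worse.

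- All women kept: difference = (μ_Y − μ_C) + (p_Y − p_C) × s
- Affected women dropped: difference = μ_Y − μ_C
- Part lost = (p_Y − p_C) × s

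If severity also differs by arm, the part lost is p_Y × s_Y − p_C × s_C.

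With no other effect (μ_Y = μ_C), all rates and shifts being assumptions:

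| Yoga rate | Control rate | Shift (SD) | Difference, all kept (SD) | Difference under the rule (SD) |
|---|---|---|---|---|
| 5% | 5% | 2 | 0.00 × 2 = 0.00 | 0 |
| 15% | 5% | 1 | 0.10 × 1 = 0.10 | 0 |
| 20% | 10% | 1 | 0.10 × 1 = 0.10 | 0 |
| 20% | 5% | 2 | 0.15 × 2 = 0.30 | 0 |
| 25% | 5% | 2 | 0.20 × 2 = 0.40 | 0 |
| 5% | 20% | 2 | −0.15 × 2 = −0.30 | 0 |

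A simulation with 1,000,000 women per arm agreed to within 0.003 SD for the rows it covered, which were all except 20% against 5%. That row follows from the formula and mirrors the last one. In a trial of 20 per arm, 20% against 5% means 4 yoga women and 1 control woman excluded.

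**4. Cut-off model (alternative assumption).** Suppose instead that a flare-up is any outcome above a cut-off c. The mean of a normal outcome with mean m and SD 1, cut off above c, is m − φ(c − m)/Φ(c − m). For a true harm of m = 0.5 SD:

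| Cut-off (SD) | Excluded, yoga | Excluded, control | Estimated harm (SD) |
|---|---|---|---|
| 1.0 | 30.8% | 15.9% | 0.28 |
| 1.5 | 15.9% | 6.7% | 0.35 |
| 2.0 | 6.7% | 2.3% | 0.42 |

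Under this model the harm is understated, not erased.

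**5. Which measurements are dropped.** The text does not say whether all of a woman's measurements go or only those after the event. The calculations above take the affected women out altogether. If only later readings go, the planned longitudinal regression keeps her earlier ones. Those precede the flare-up, however, and carry its effect only as far as they predict it. At visits after the event the readings are still missing because of the outcome. Both versions are outcome-dependent; the size may differ.

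**The case against.** The best defence is that the rule guards against treatment started during the trial. Women with an event are sent for medical help, and treatment beyond self-management is an entry exclusion because it would affect the results. Readings taken after treatment may reflect that treatment, and could even mask the flare-up. This stands as a reason for a sensitivity analysis. It does not justify removing randomised women from the main comparison, and the rule as written acts on the event whether or not treatment followed.

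The trial is also a small pilot, and the article reports that earlier exercise trials saw no exacerbation, which suggests low rates. With equal rates and severity the fixed-shift bias is zero. That limits what can be said about size. It does not make the rule sound, because the article states effectiveness aims and means its methods to inform larger trials.

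Four stronger readings are tempting and are not supported:

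- *The rule deletes the primary and safety outcome, so yoga would be reported as safe.* It drops the measurements of affected women only. Adverse events go to the ethics committee, and nothing prevents counts of flare-ups and infections by arm from being reported.
- *Weekly classes mean that flare-ups are noticed more often in the yoga arm.* This is an inference. The teacher is given no role in detecting them, and blinded assessors measure both arms at the same weeks. If the worst 15% of yoga and 5% of control women were removed with no true effect, the spurious benefit would be 0.2743 − 0.1086 = 0.17 SD (20% against 5%: 0.3500 − 0.1086 = 0.24 SD). That arithmetic is right, but it rests wholly on this unsupported difference in detection.
- *The statement to women discourages reporting.* It may, but the text can be read as being told only once the event has occurred.
- *A second exclusion takes an arm below its target.* This is true against the upper figure of 19. Against 13 there is room for seven.

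**Conclusion.** The point holds. The article fixes a post-randomisation exclusion on eligibility grounds, and one of its two triggers is a worsening of the primary outcome. This is a stated rule, not a detail left to an analysis plan. It can hide harm or benefit in the efficacy comparison whenever flare-up frequency or severity differs by arm.

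The size cannot be derived from the documents. Under the fixed-shift assumption it runs from zero (equal rates and severity) to 0.30 SD for 20% against 5% with a 2 SD rise and 0.40 SD for 25% against 5%, in either direction. Under the cut-off assumption a harm of 0.5 SD would be estimated at 0.28 to 0.42 SD. These are illustrations, not forecasts. The case for changing the rule rests on its dependence on the outcome, not on any one of these figures.

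**What to change.** - Delete the exclusion rule, and the matching statement to women that their measurements will not be used.
- State that every randomised woman is analysed in her allocated group with all available measurements, including those after an infection or flare-up. The comparison then describes assignment to yoga or control, together with whatever treatment followed an event.
- Report infections and flare-ups by arm alongside the efficacy results.
- Keep an analysis without post-event measurements only as a labelled sensitivity analysis, because treatment for the event may itself change the readings. State there which measurements are left out.

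**Cost.** A wording amendment to the protocol and to what women are told, and some added outcome variance from the retained readings. The article says that affected women may continue but not expressly that they are still measured, so the amendment should say that their scheduled measurements are taken. The change concerns analysis and reporting; it leaves the advice to seek medical help as it is.

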### Withdrawal from study

Participants will be able to withdraw from the trial at any time without prejudice, as set out in the information sheet distributed at the time of consent.

### Identification of eligible participants

Recruitment will occur over a two-month period throughout Tasmania. Key people, including professionals in the field of lymphoedema and relevant organisations such as the Cancer Council and Breast Screen, and support and exercise groups such as Encore and Dragons Abreast, will be contacted and asked to disseminate information about the trial to potential participants, through flyers and posters.

Media exposure will be sought, including articles in local newspapers and interviews on local radio. Posters will be put in major and rural hospitals, Women’s Health Centres (Hobart, Launceston) and Community Centres.

Individuals interested in participating will be asked to contact the principal investigator (AL) who will outline the study, including the yoga intervention, the home-practice, the methods and dates of measurement, after ascertaining if they are suitable for participation as per the inclusion and exclusion criteria. Eligible participants will be sent an information sheet and informed consent form. After receiving the forms, they will be telephoned in order to discuss any questions or concerns about the trial before returning the signed consent form.

After the signed consent form is returned, participants will be sent the dates for the trial (measurements and intervention) as well as a questionnaire with demographic and medical information to be completed and brought to baseline measurement. At this time, the manual for current best-practice will also be sent, and followed by another phone call to check for clarity.

### Sample size calculation

An *a priori* sample size calculation based on clinically significant changes between groups of between 10-20% in primary outcome measures with standard deviations of between 12 and 15% of the mean, or within groups 10% difference with an SD of 20%, indicated that numbers of between 13 and 19 participants would be required per group. Consequently, we plan on recruiting 20 participants per group to allow for a small number of withdrawals.

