### Data analysis

Medical and demographic information will be analysed using descriptive analysis within SPSS (version 19SPSS Inc. IBM, USA 2010) to calculate means and standard deviations or percentage values. Differences between groups will be assessed using t-tests for comparing continuous variables and chi-square tests for categorical variables.

All statistical analyses for quantitative measurements will be performed using STATA statistical software (version 12; 1985-2011; STATA corp.; College Station; Texas, USA). Binary categorical data will be analysed for variability between the groups using logistic regression. Parametric longitudinal data will be analysed via mixed methods linear regression. Non-parametric data will use ordinal logistic regression. Post-hoc testing will be performed on both parametric and non-parametric data using the Holms test to locate the means that are significantly different. Statistical significance will be set at p < 0.05.

Qualitative data from interviews will be analysed using an iterative-thematic approach.

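### The stated 13 to 19 women per group does not follow from the between-group inputs, which span 7 to 37 at 80% power; a 10% difference is not shown to be covered

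*Protocol article*

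**What the plan says.** The section Sample size calculation gives two alternative sets of inputs and one result.

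- Between groups: "clinically significant changes between groups of between 10-20% in primary outcome measures with standard deviations of between 12 and 15% of the mean".
- Within groups: "within groups 10% difference with an SD of 20" (per cent).
- Result for both: the calculation "indicated that numbers of between 13 and 19 participants would be required per group".
- Recruitment: "we plan on recruiting 20 participants per group to allow for a small number of withdrawals".

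The Abstract gives the same total: "a total of 40 women receiving either yoga intervention or current best practice care". The sample size section names no power, significance level, sidedness, formula or correlation. The only significance level is in Data analysis: "Statistical significance will be set at p < 0.05", again without sidedness. That section plans a mixed linear regression for longitudinal data.

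**The concern.** The paragraph prints inputs and an output that can be checked against each other, and they disagree. A reader will take it that about 20 women per group suffice for any difference from 10% upward, because the whole 10-20% range is called clinically significant and is tied to a requirement of at most 19. If the lower end in fact needs more than 20, the only justification given for the trial's size claims more than its figures show. The margin is also thin: 20 against 19 allows for one withdrawal per group (1/20 = 5%). Under Ethical considerations, women with an infection or flare-up also have their measurements left out of the results.

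**Working it through.** **Inputs.** From the article: difference d = 10% to 20%; SD s = 12% to 15% of the mean; equal groups of 20; p < 0.05. Assumed, because not stated: two-sided test, 80% power, unadjusted two-sample t-test at one time point.

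**Attempt to reproduce 13 to 19.** The normal approximation is n per group = 2 (1.960 + 0.842)² (s/d)² = 2 × 7.849 × (s/d)². The exact t-test adds about one woman per group.

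| d | s | 2 × 7.849 × (s/d)² | rounded up | exact t-test |
|---|---|---|---|---|
| 10% | 12% | 15.70 × 1.44 = 22.6 | 23 | 24 |
| 10% | 15% | 15.70 × 2.25 = 35.3 | 36 | 37 |
| 20% | 12% | 15.70 × 0.36 = 5.7 | 6 | 7 |
| 20% | 15% | 15.70 × 0.5625 = 8.8 | 9 | 10 |

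The inputs span 7 to 37. The stated range is not reproduced.

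**Does another setting rescue it?** Spans by exact t-test over the same inputs:

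- two-sided: 8 to 42 (85% power), 9 to 49 (90%), 11 to 60 (95%);
- one-sided: 6 to 29 (80%), 7 to 40 (90%).

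Single ends can be matched, but under different settings: 10% with SD 12% gives 19 if one-sided at 80% power, and 20% with SD 15% gives 13 if two-sided at 90% power.

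There is a general reason. Power, sidedness and a common baseline correlation all multiply (s/d)² by one constant. The closest that a 10% case and a 20% case can come is 10%/SD 12% against 20%/SD 15%, a ratio of 1.44/0.5625 = 2.56. The stated range has a ratio of 19/13 = 1.46. Small-sample corrections and rounding shift this only a little (24/10 = 2.4 in the table).

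**What does give 13 and 19.** A single difference with SD 12% and 15%: 14.2% (two-sided, 80% power) or 15% (two-sided, 85% power). A 10% difference also gives 13 and 19, but only at about 50% power.

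**Within-group route.** With the 20% read as the SD of the differences, a paired t-test at 80% power needs 34 (two-sided) or 27 (one-sided). If 20% is instead the SD of a single measurement, an assumed correlation of 0.7 gives 21 and 0.8 gives 15, but the article states no correlation.

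**Power for a 10% difference.** The noncentrality is (d/s)√(n/2). With n = 20 it is (10/12) × √10 = 2.64, or (10/15) × √10 = 2.11, against a critical t of 2.02 on 38 degrees of freedom.

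| Evaluable per group | Power, SD 12% | Power, SD 15% | Detectable at 80% power, SD 12% to 15% |
|---|---|---|---|
| 20 | 73% | 54% | 10.9% to 13.6% |
| 19 | 70% | 52% | 11.2% to 14.0% |
| 17 (15% loss assumed: 20 × 0.85) | 65% | 47% | 11.9% to 14.9% |

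The 20% end is well covered: with 20 per group, power is at least 98%.

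**The case against.** **Pairing.** There are several primary outcomes, and the two ranges may span outcomes that each have their own difference and SD. Crossing the smallest difference with the largest SD makes a pair that the text never states. That is fair, and interior pairs do give 13 to 19. It does not save the stated range: at two-sided 5% and 80% power, any pair containing 10% needs at least 24, and any pair containing 20% needs at most 10.

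**The test.** The unadjusted single-time comparison is an assumption, and the plan is a mixed model over repeated measurements. With baseline adjustment and an assumed correlation of 0.7, the variance is multiplied by 1 − 0.7² = 0.51, and a 10% difference needs 13 (SD 12%) or 20 (SD 15%) per group, close to the stated figures. This stands as a limit on the power statement. A reader might infer that the trial will miss a true 10% effect in a quarter to a half of cases; the article does not support that, because those rates belong to a simpler analysis than the one planned. Nor does it follow that 37 per group are needed. Equally, no correlation is stated, and with 0.7 the 20% end falls to 5 or 6, so 13 to 19 is still not the result for 10-20%.

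**Pilot.** The Abstract calls this a pilot that will inform larger trials. That softens the consequence but not the arithmetic, since the article presents an a priori calculation for clinically significant differences.

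**Conclusion.** The mismatch between inputs and result holds, and it does not depend on the assumed power or sidedness. The figures of 7 to 37 per group, and of 73% and 54% power at 20 per group, do rest on two-sided 5% and an unadjusted t-test, and the 7 to 37 also on 80% power. On that basis the lower end of what the plan calls clinically significant is not shown to be covered by 19 or 20 per group. It may be covered under the mixed model, but nothing in the article demonstrates it.

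Two stronger readings are not supported. It would be wrong to say that no significance level is given: Data analysis sets one, and what is missing is power and sidedness. It is also only a possibility that a non-significant result would be reported as absence of a worthwhile effect; the article sets no such rule.

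**What to change.** Enrolment and conduct stay as they are. Rewrite the sample size paragraph to:

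1. State the power, sidedness, formula, the difference-SD pair or pairs and any correlation actually used.
2. Replace the 10-20% claim with the difference that the planned size can detect. If the calculation was unadjusted, two-sided 5% with 80% power, that is about 11% (SD 12%) to 14% (SD 15%) with 19 or 20 evaluable women per group, and 12% to 15% with 17 if 15% are lost. If another setting or a stated correlation was used, give the figures for that.
3. Not imply that 10% is covered unless a stated correlation supports it.
4. Commit to reporting between-group differences with 95% confidence intervals set against the 10% threshold.

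The cost is one reworded paragraph and a stated detectable difference that looks less favourable than the present text.
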